**Table 4 Tab4:**
[figure not shown]
SSC6 Versus Silbernagel’s rehabilitation program.

### Statistical analysis and power calculation

This study is powered to detect a change of 15 points on the VISA-A questionnaire, similar to previous studies investigating clinical changes after a rehabilitation program [61, 62]. The average reported change in a VISA-A questionnaire after a 12-week intervention is 21 points with a standard deviation 6.6 points [44]. Assuming a power of 80% and a two-sided 5% significance level, a total of 25 participants in each group would be required. Allowing for a conservative drop-out rate of 15%, the proposed total sample size is 60, with 30 in each group. This number is similar to those used in other high quality injury rehabilitation RCT studies [40, 45].

Statistical analysis will be performed using R (R Studio version 1.2.5). Descriptive statistics will be used for all continuous variables, and means and standard deviations will be reported. Comparisons between both groups at different timepoints will be assessed using Student’s independent samples two-tailed t-tests. An intention to treat analysis will be used to test a within-group and between-group change in VISA-A questionnaire score at testing and follow-up timepoints, using a repeated measures Analysis of Covariance (ANCOVA). The primary outcome measure - changes to the VISA-A questionnaire, will the dependent variable, group will the between participants factor and time will be the covariate. Non-parametric equivalents (Matt-Whitney U-Test and Friedman Test respectively) will be used if a Shapiro-Wilk test indicates that the assumption of normality has not been met. A multiple regression analysis will be used to investigate the total variance and the relative weight of each independent variable with changes in VISA-A score as the dependent variable. The independent variables will be changes in plantar flexor strength, reactive strength and lower limb biomechanical variables, as well as exercise adherence and fidelity. Effect sizes will be reported using partial eta squared threshold values of > 0.2 (small), > 0.5 (moderate), and > 0.8 (large). Statistical significance will be accepted at α = 0.05.

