### Primary outcome measure

#### VISA-A questionnaire

The VISA-A questionnaire has been shown to be a valid, reliable and easy-to-use outcome measure tool for intervention studies on AT [46]. It consists of eight questions regarding pain and function during both daily living and sporting activities. The overall score is between 0 and 100 where higher scores represent reduced pain and improved function. An improvement of 21 points between 2 and 12 weeks of a rehabilitation program have been typically observed [44]. While the VISA-A score will not determine eligibility for inclusion into the study, it will be used to map progress over the course of the rehabilitation program and in the follow-up period. The difference in VISA-A score between both training protocols from baseline testing to the outcome testing at 6 weeks, 12 weeks, 3, 6 and 12 months; will formulate the primary outcome measure for this study.

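### The stated inputs (15 points, SD 6.6, 80% power, two-sided 5%) require about 5 participants per group, not 25, so the effect the trial is sized to detect is unknown

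*Protocol article*

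**What the plan says.** Everything relevant stands in the first paragraph of Statistical analysis and power calculation in the protocol article.

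- Target: "This study is powered to detect a change of 15 points on the VISA-A questionnaire".
- Variability: "The average reported change in a VISA-A questionnaire after a 12-week intervention is 21 points with a standard deviation 6.6 points". This is the only SD given for the VISA-A.
- Error rates and result: "Assuming a power of 80% and a two-sided 5% significance level, a total of 25 participants in each group would be required".
- Inflation: "Allowing for a conservative drop-out rate of 15" per cent, after which "the proposed total sample size is 60, with 30 in each group".

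The VISA-A questionnaire section repeats the 21-point figure from the same source (reference 44): "An improvement of 21 points between 2 and 12 weeks of a rehabilitation program have been typically observed". The Background cites that reference among the evidence for the programme chosen as comparator. The article gives no other SD, planning effect size, correlation or multiplicity adjustment. The planned group comparisons are two-tailed independent-samples t-tests, with a repeated measures ANCOVA for the VISA-A.

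**The concern.** A target more than twice the SD is a very large standardised effect, and a two-group comparison of means needs only a handful of participants to detect it. A requirement of 25 per group suggests that some other SD or some other difference was used.

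This matters for reading the result. If the SD really is near 6.6, the trial can detect about 5 points, and a null result would argue against any but small differences. If the SD is near 18.5, the trial has 80% power only for differences of 15 points or more, and smaller differences could easily be missed.

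The word used for the target adds to the doubt. The trial's question is a comparison of two active programmes, but a change of 15 points can be read as improvement within a group. If 15 points is the between-group difference, and the comparator repeats the cited 21-point improvement, the SSC6 arm would have to improve by about 21 + 15 = 36 points. The paragraph does not say that this is what is being assumed.

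**Working it through.** **Inputs** (all from Statistical analysis and power calculation): difference 15; SD 6.6; two-sided alpha 0.05; power 80%; equal allocation; dropout 15%. Stated result: 25 per group, 30 after dropout.

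**1. The plan's figure from its own inputs.** The normal approximation for two means is

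n per group = 2 × (z for alpha + z for power)² × (SD / difference)²

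= 2 × (1.96 + 0.842)² × (6.6 / 15)² = 3.04, so 4 per group.

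The standardised effect is 15 / 6.6 = 2.27. At this effect the exact t-test (noncentral t) has 76% power with 4 per group and 88% with 5, so 5 per group are required. The stated 25 is not reproduced.

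**2. Dropout step.** 25 / 0.85 = 29.4, so 30 per group and 60 in total. This step is correct; the fault lies in the 25.

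**3. Other readings of the inputs** (normal approximation, then exact t):

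| Reading | n per group |
|---|---|
| One-sided 5%, 80% power | 3, 4 |
| 90% power | 5, 6 |
| 95% power | 6, 7 |
| SD × √2 for a change score | 7, 8 |
| Bonferroni for six comparisons (alpha 0.05/6) | 5, 7 |
| Difference 21 instead of 15 | 2, 3 |
| Difference 6 (21 − 15), 80% power | 19, 21 |
| Difference 6, 90% power | 26, 27 |

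None gives 25. The difference of 6 comes nearest but abandons the stated 15 points, and at 90% the stated power as well. Reading 25 as the total (12.5 per group) gives a detectable difference of 7.7 points at SD 6.6, which is not 15 either.

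**4. Working back from 25 per group.** At 80% power and two-sided 5%, the t-test detects a standardised effect of 0.809.

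- At SD 6.6: 6.6 × 0.809 = 5.3 points.
- For 15 points: 15 / 0.809 = SD 18.5 (18.9 by the normal approximation).

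For comparison, a generic standardised effect of 0.8 gives 2 × (1.96 + 0.842)² / 0.8² = 24.5, so 25 by the normal approximation, and 26 by the exact t-test. That may be where 25 came from, but the article does not say so, and nothing here depends on it.

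**5. Power for 15 points with 25 per group** (t-test):

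| SD | Power |
|---|---|
| 6.6 (stated) | above 99.99% |
| 18.5 (back-calculated) | 80% |
| 20 (assumed) | 74% |
| 22 (assumed) | 66% |
| 25 (assumed) | 55% |

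**The case against.** The strongest reply is that on its stated inputs the trial is over-sized: with 25 per group and SD 6.6 it has far more than 80% power for 15 points, so no participant is exposed to an underpowered comparison. That is correct as far as it goes. What is false is that 25 are required. But the reassurance holds only if 6.6 is the right SD, and 25 itself suggests that a different SD or difference was used.

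Second, the article does not say outright that 6.6 was the planning SD. It takes 15 points from two references and the 21 (SD 6.6) from another, so the real SD may have been lost in condensing. This stands as a possible explanation, but it does not clear the text. The paragraph would then print an SD that was not used and omit the one that was.

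Third, the back-calculated bounds assume 25 completers per group and an unadjusted t-test. If all 30 per group were retained, the detectable difference at SD 6.6 would be 4.9 points, and the largest SD allowing 80% power for 15 points would be 20.4. The planned ANCOVA could also change precision. The bounds are therefore conditional, but the gap between 5 and 25 is far too wide for these refinements to close.

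Fourth, the 36-point figure depends on reading 15 as a between-group difference and on the comparator repeating the cited 21-point improvement. Both are conditions, and the arithmetic mismatch does not rest on them.

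**Conclusion.** The concern holds. The stated difference, SD, power and sample size cannot all be true together: the first three give 4 to 5 per group, about a fifth of the stated 25. With 25 per group, the design has 80% power either for about 5.3 points at SD 6.6, or for 15 points at an unstated SD of about 18.5. The text does not let the reader choose between these.

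The conclusion rests on a two-group comparison of means at equal allocation and on 6.6 being the only SD given. It does not show that the trial is underpowered; that would depend on the true SD, and the powers at SD 20, 22 and 25 are illustrations based on assumed values. As this paragraph is the only justification of the sample size for the primary outcome, it must be corrected.

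**What to change.** Keep N = 60 and rewrite the paragraph.

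1. Define the target as the between-group difference in VISA-A change from baseline to week 12, the time point to which the cited 21 (SD 6.6) refers.
2. Then do one of the following:
   - (a) Report the SD actually used, with its source. For 25 per group and 15 points it has to be about 18.5. It should come from the original calculation or from data, not be solved for afterwards and then given a citation.
   - (b) Keep SD 6.6 and state that 25 per group gives 80% power for a between-group difference of about 5.3 points.
3. If 15 points is retained as the between-group target, say that it is on top of the improvement of about 21 points expected in the comparator.

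The cost is one reworded paragraph and no additional participants. The stated detectable effect may look less favourable than it does now.

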## Abstract

**Background:**

Achilles tendinopathy (AT) is a common overuse injury in running-related sports where patients experience pain and impaired function which can persist. A graded rehabilitation program has been successful in reducing pain and improving function to enable a return to sport. The aim of this study is to compare the effectiveness of a criteria-based rehabilitation program including strength and reactive strength targets, with a previously successful rehabilitation program on changes in pain and function using the Victorian Institute of Sport Assessment-Achilles (VISA-A) questionnaire. Secondary aims will be to assess changes in calf strength, reactive strength, and lower limb running and forward hop biomechanics over the course of a 12-week rehabilitation program, and long-term follow-up investigations.

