### Outcome measures and assessments

#### Investigations

At baseline, week 6 and 12, all participants will be required to complete a VISA-A questionnaire as well as perform isokinetic testing and 3D motion capture running gait assessment. In addition, hop testing will be performed at week 6 and 12 [see Table 3]. Hop testing is included in the testing battery from week 6 onwards as it is expected some participants with Achilles pain at baseline testing may be fearful of performing hopping tasks or risk of exacerbating their pain, and the data collected may not be an accurate reflection of their capabilities.

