#### Three-dimensional running gait analysis

Altered running biomechanics and muscle recruitment strategies have been highlighted in runners with AT [49–52]. Using a proprietary three-dimensional optical motion analysis system (Run 3D, Oxford, United Kingdom) the following kinematic and spatiotemporal variables will be measured: contact time, aerial time, stride length, stride frequency and joint angular displacements from initial contact to mid stance phase. Lower limb stiffness will be calculated using a validated equation based on the spring-mass model with running speed, contact time, body mass and leg length as inputs [53]. The participants will warm-up by running for between 2 and 5 min on the treadmill at a self-selected speed. Once they report that they are adequately warmed up they will be instructed to run at a speed that they feel they would be comfortable running at a steady pace for 30 min. Data will be captured for 30 s at a random interval over a 2 min period and the participants will not be informed about when the data capture begins. For the subsequent tests at week 6 and 12, the participants will be required to repeat the same speed for re-analysis.

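### Isokinetic torque and running gait are measured at baseline, but the only stated between-group test for them has no baseline covariate, which gives away precision

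*Protocol article*

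**What the plan says.** All places are in the protocol article.

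- **Statistical analysis and power calculation** gives one general between-group method: "Comparisons between both groups at different timepoints will be assessed using Student’s independent samples two-tailed t-tests". If normality is rejected, a Mann-Whitney test takes its place. No outcome is named, no covariate is listed, and the text does not say whether visit values or changes from baseline are compared.
- The same section confines the ANCOVA to VISA-A. It covers "within-group and between-group change in VISA-A questionnaire score at testing and follow-up timepoints, using a repeated measures Analysis of Covariance (ANCOVA"), and in it "group will the between participants factor and time will be the covariate".
- The multiple regression uses the secondary measures only as predictors of VISA-A change: "The independent variables will be changes in plantar flexor strength, reactive strength and lower limb biomechanical variables, as well as exercise adherence and fidelity". It does not compare the groups on those measures.
- **Investigations** and Table 3 put strength and gait at weeks 6 and 12 as well as at baseline: "all participants will be required to complete a VISA-A questionnaire as well as perform isokinetic testing and 3D motion capture running gait assessment". Hop testing starts later: "In addition, hop testing will be performed at week 6 and 12".
- **Three-dimensional running gait analysis** lets each participant pick a comfortable steady speed at the first test and then fixes it: "For the subsequent tests at week 6 and 12, the participants will be required to repeat the same speed for re-analysis". Running speed is also an input to the stiffness calculation there.
- The **Abstract** words the secondary objective in terms of change: "Secondary aims will be to assess changes in calf strength, reactive strength, and lower limb running and forward hop biomechanics".

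**The concern.** Once VISA-A has the ANCOVA and the regression has its separate purpose, the t-test (or its Mann-Whitney fallback) is the only stated between-group comparison that can cover peak torque and running gait. Read naturally, a comparison at different timepoints uses the values at each visit. Such a test ignores the baseline measurement that the trial already collects.

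People differ persistently in plantar flexor strength and running style, and that spread goes into the error term. For the running variables, part of the spread at week 12 comes from the speed each person chose at the start. Speed is constant within a person, so the baseline value, taken at the same speed, would absorb much of that spread. The stated test does not use it.

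At stake is how small a difference in strength or gait a trial of 60 participants can show.

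**Working it through.** **Inputs**

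- n = 25 per group, two-sided 5%, 80% power: Statistical analysis and power calculation.
- Baseline to follow-up correlation rho for torque and gait: not given in the documents. Assumed range 0.3 to 0.8.
- Outcomes are in SD units, with the same SD at baseline and follow-up (assumption).

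**The plan's own figure.** The 25 per group is used here only as a number of completers. The dropout step reproduces: 25/0.85 = 29.4, rounded up to 30 per group and 60 in total. The 25 does not follow from the stated 15 points and SD 6.6: 2 × (1.96 + 0.84)² × (6.6/15)² = 3.04, so 4 per group. It fits a standardised difference of about 0.8. That is a separate VISA-A matter and does not affect this point. No secondary outcome has its own power calculation.

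**Variance of the group difference, relative to a t-test on visit values**

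- t-test on visit values: 1
- t-test on changes: 2(1 - rho)
- ANCOVA on baseline: 1 - rho²

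The change-score factor minus the ANCOVA factor is 2(1 - rho) - (1 - rho²) = (1 - rho)², which is never negative. So ANCOVA is at least as precise as a change-score test, apart from one degree of freedom. The change-score test is worse than the plain t-test when 2(1 - rho) > 1, that is, when rho < 0.5.

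**Detectable difference.** With 25 per group, the two-sample t-test has 80% power at 0.809 SD (noncentral t). After adjustment this becomes 0.809 × sqrt(1 - rho²). The last column is the size at which an unadjusted test would match 25 per group adjusted, 25/(1 - rho²).

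| rho (assumed) | ANCOVA factor | Change-score factor | Detectable, adjusted (SD) | Power, adjusted, at 0.809 SD | Equivalent unadjusted n per group |
|---|---|---|---|---|---|
| 0.3 | 0.91 | 1.40 | 0.77 | 83.6% | 27.5 |
| 0.5 | 0.75 | 1.00 | 0.70 | 89.9% | 33.3 |
| 0.7 | 0.51 | 0.60 | 0.58 | 97.5% | 49.0 |
| 0.8 | 0.36 | 0.40 | 0.49 | 99.7% | 69.4 |

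**Simulation check.** With rho = 0.7, a true difference of 0.5 SD, 25 per group and 4,000 runs, power was 41% for the t-test and 68% for ANCOVA.

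**Error rate.** Baseline testing precedes randomisation, so expected baselines are equal. The expected week-12 difference in values then equals the expected difference in change, and the t-test rejects 5% of the time under no effect. Conditional on the observed imbalance, the rate moves both ways. With a 0.5 SD baseline difference (chance about 7.7% per outcome, either direction) it is 10.8%, 15.6% and 18.2% at rho 0.5, 0.7 and 0.8. With exactly balanced baselines it is P(|Z| > 1.96/sqrt(1 - rho²)) = 2.4%, 0.6% and 0.1%. These average out to 5%.

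**The case against.** The strongest reply is that the sentence fixes less than the concern needs. It names no outcome and may mean changes, a quantity that the same section uses in the regression. A t-test on changes would use the baseline and cancel much of the stable speed effect. This is right as a reading of the text: that the sentence covers torque and gait is inferred from the ANCOVA being limited to VISA-A. It does not remove the point, because the adjusted comparison is at least as precise under either reading.

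Other parts of the reply also stand:

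- A reader might infer that the test produces false positives or answers the wrong question. The documents do not support that. Allocation is randomised after baseline testing, so the test is valid for the same contrast, and the rates of 11% to 18% hold only given a chosen imbalance.
- A reader might take the aim to be superiority of SSC6 on strength or gait. The Abstract speaks only of assessing changes, and the Aims section asks whether those changes go with VISA-A improvement.
- Torque is scaled to body mass, and asymmetry uses the participant's other limb as reference. Some stable variation is therefore already removed, and rho may sit lower in the range for these measures.
- Fixing speed within a participant is sound control, not a design flaw. With baseline in the model, speed as a further covariate is largely redundant.

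It may also be said that covariates are a detail left to an analysis plan. Here, however, the article states a method, and the method can be improved at almost no cost.

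**Conclusion.** The point holds as a loss of precision on secondary outcomes. It is not a bias, and it does not touch the VISA-A analysis. The stated between-group method for peak torque and running gait carries no baseline covariate although the baseline is measured. Adjustment would multiply the error variance by 0.91 to 0.36 over an assumed rho of 0.3 to 0.8, and lower the detectable difference at 25 per group from 0.81 SD to between 0.77 and 0.49 SD. The direction holds for any non-zero rho, apart from the trivial loss of a degree of freedom. The size depends on rho, which the documents do not give, and at rho 0.3 the gain is small: 3.6 points of power. The sentence also leaves open whether values or changes are compared, and that should be settled at the same time.

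**What to change.** Replace the t-test for the outcomes that have a baseline, and keep it for those that do not:

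- **Peak torque (both knee positions), between-limb asymmetry and each running variable:** ANCOVA, or one mixed model over weeks 6 and 12 with group, visit and group-by-visit. Enter the participant's own baseline value of that variable as covariate. Report the adjusted week-12 difference between groups with its 95% confidence interval.
- **Running variables:** test speed may be added as a covariate. This is optional and probably brings little once baseline is in the model.
- **Hop tests:** keep the unadjusted comparison, because they have no baseline.

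The cost is a change of wording in the analysis section and one or two degrees of freedom. The baseline values are already collected, and the speed must be known in order to be repeated. No extra participants or visits are needed.

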### Randomisation and blinding

Participants will be assessed at baseline before being randomly assigned to the intervention group or control group and will follow a prescribed rehabilitation program for 12 weeks. See Table 3 for a summary of the study design. The randomisation will be performed using the online tool www.sealedenvelope.com and the participant will be handed an envelope from an independent observer not involved with the study, containing their respective group allocation number. The principal investigator and training group investigators will be blinded to the group randomisation process. These procedures have been used in similar studies [45]. The participants will be prescribed with an exercise program with video demonstrations of each exercise under the supervision of the investigator in their respective group. The program will be carried out at home or in a local gym in addition to supervised rehabilitation sessions every 2–3 weeks at SSC. Testing will take place again at week 6 and 12. Follow-up interviews will take place at 6, 12 and 24 months after baseline testing. The investigator involved with the testing and follow-up interviews will also be blinded to the group allocation. The primary outcome measure will be changes to the VISA-A questionnaire. Secondary outcome measures will include plantar flexor strength, lower limb reactive strength, biomechanics and running gait.

**Table 3 Tab3:** Overview of outcome measures over the course of the study

	Baseline	Week 6	Week 12	6 months	12 months	24 months
Body mass	X					
Body height	X					
Body mass index	X					
Sport/activity level	X			X	X	XX
VISA-A Questionnaire	X	X	X	X	X	X
Isokinetic plantar flexor peak torque (knee extension)	X	X	X			
Isokinetic plantar flexor peak torque (knee flexion)	X	X	X			
3D running gait analysis	X	X	X			
Double leg drop jump		X	X			
Single leg drop jump		X	X			
Single leg horizontal rebound		X	X			
Exercise compliance		X	X	X		

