Our study will include a sample of participants who practise running-based sports and are of a particular age profile (age 18–45), have had no injection therapies in the previous 6 months and no co-existing lower limb injuries. Like most studies of similar design, there is a high risk of drop-outs, poor compliance with the respective programs and failure to respond to the follow-up questionnaires. This will be managed by aiming for a higher number of participants than the study is powered for and maintaining regular communication with the participants.

In summary, this two-arm RCT will compare the effectiveness of a criteria-based rehabilitation program with progression guided by achieving functional outcome measures with an evidenced-based program where progression is guided solely by pain symptoms. The results of this study will provide insights as to whether improved strength, reactive strength and lower limb biomechanics are associated with reduced pain in patients with chronic mid-portion AT and assist clinicians treating this injury to set objective criteria to progress rehabilitation and return to sport.

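### The primary repeated measures ANCOVA, as written, tests one visit-averaged group difference and uses baseline VISA-A only through the change score; a week-12 contrast adjusted for baseline would match the sample size and be more precise than the unadjusted week-12 comparison

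*Protocol article*

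**What the plan says.** The protocol article, under Statistical analysis and power calculation, sets out the analysis of the primary outcome:

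- **Purpose and population.** "An intention to treat analysis will be used to test a within-group and between-group change in VISA-A questionnaire score at testing and follow-up timepoints", by repeated measures ANCOVA.
- **Roles in the model.** Change in VISA-A is the dependent variable, and "group will the between participants factor and time will be the covariate". Time is the only covariate named.
- **Comparisons at single visits.** "Comparisons between both groups at different timepoints will be assessed using Student’s independent samples two-tailed t-tests".
- **Fallback if normality fails.** "Non-parametric equivalents (Matt-Whitney U-Test and Friedman Test respectively) will be used".
- **Sample size.** The inputs are a 15-point change and the average change and SD reported after a 12-week intervention. They give 25 per group, raised to 30 for 15% drop-out.

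Table 3 schedules VISA-A at baseline and at five later visits: week 6, week 12, and 6, 12 and 24 months. The VISA-A questionnaire section defines the outcome as the difference between programs "from baseline testing to the outcome testing at 6 weeks, 12 weeks, 3, 6 and 12 months; will formulate the primary outcome measure", without singling out one visit. The Discussion accepts that "there is a high risk of drop-outs, poor compliance with the respective programs and failure to respond to the follow-up questionnaires". The remedies it offers are over-recruitment and regular contact with participants.

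**The concern.** In a repeated-measures design, visit is the within-participant factor. Placed as a covariate beside group, with no interaction stated, it leaves a single group coefficient: the difference in change averaged over all post-baseline visits. The sample size rests on a 12-week quantity, so the model and the design calculation address different targets unless the effect is the same at every visit. The t-tests do give visit-specific comparisons, but they stand outside the model, do not adjust for baseline, and none is named as the deciding one. A reader cannot tell which result will settle the primary question.

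The method is called ANCOVA, yet the usual covariate, the baseline score, is not in it. Baseline VISA-A is scheduled for everyone, so precision that costs nothing to obtain is given up.

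The analysis is labelled intention to treat in a trial that expects substantial drop-out and non-response, but nothing in the description of the model says how a participant with a missing visit contributes.

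**Working it through.** **Inputs from the protocol.** Difference 15 points; SD 6.6; power 80%; two-sided 5%; 25 per group; 15% drop-out; 60 in total; five post-baseline VISA-A visits.

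**The plan's own figure.** n per group = 2 × (1.96 + 0.84)² × 6.6² / 15² = 15.68 × 43.56 / 225 = 3.04, so 4 per group (5 with the t distribution), not 25. The drop-out step does reproduce: 25 / 0.85 = 29.4, so 30 per group. The failure to reach 25 is a separate matter and neither supports nor weakens this point. It does mean that an SD has to be assumed below. I use 18.5, the SD of change at which 25 per group gives 80% power for 15 points with a t-test.

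**Step 1: precision from baseline.** Assume equal variance σ² at baseline and follow-up, with correlation r.

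- Variance of the change score: 2σ²(1 − r).
- Residual variance after adjusting for baseline: σ²(1 − r²).
- Ratio: (1 − r²) / [2(1 − r)] = (1 + r)/2.

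Power at week 12 for 15 points, 25 per group, t distribution (unadjusted change score: SE = 18.5 × √(2/25) = 5.23, power about 80%):

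| Assumed r | Variance ratio | Reduction | Adjusted SD = 18.5 × √ratio | Power, adjusted |
|---|---|---|---|---|
| 0.3 | 0.65 | 35% | 14.9 | about 94% |
| 0.5 | 0.75 | 25% | 16.0 | about 90% |
| 0.7 | 0.85 | 15% | 17.1 | about 86% |

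The ratio is below 1 for every r below 1, so the direction does not depend on the assumed values.

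**Step 2: what averaging over visits does.** Assume r = 0.5 between every pair of scores. Then σ = 18.5, because 2σ²(1 − 0.5) = σ². The mean of five change scores has variance σ²[(1 − r) + (1 − r)/5] = 0.6σ², an SD of 14.3 and, at 25 per group, an SE of 14.3 × √(2/25) = 4.05.

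| Assumed effect at week 6, week 12, 6, 12, 24 months | Average | Power of averaged test |
|---|---|---|
| 7.5, 15, 7.5, 0, 0 | 6.0 | about 31% |
| 7.5, 15, 7.5, 3.75, 0 | 6.75 | about 37% |
| 7.5, 15, 15, 15, 15 | 13.5 | about 90% |
| 15 at every visit | 15.0 | about 95% |

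Under these assumptions the averaged test matches the unadjusted week-12 test when the average effect is 15 × √0.6 = 11.6 points. It matches the baseline-adjusted week-12 test at 15 × √(0.6/0.75) = 13.4 points. Below those values averaging loses power; above them it gains.

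**Step 3: incomplete participants.** The text supports two ways of fitting the model, with different consequences.

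- Partial eta squared and the Friedman fallback suggest a classical analysis on complete cases. Friedman needs complete blocks and has no between-group factor. At 15% drop-out, 60 × 0.85 = 51 participants would remain. If 5% or 10% were missed independently at each of five visits (assumed), 60 × 0.95⁵ = 46 or 60 × 0.90⁵ = 35 would be complete.
- Time as a covariate suggests one row per visit, which keeps anyone with at least one follow-up score. In a simulation with 15% drop-out, such a fit used 58.2 of 60 participants on average, against 51.2 complete cases.

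The protocol does not say which applies.

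**The case against.** Four replies have force.

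1. **Baseline is used.** The outcome is change from baseline, so the baseline difference is removed with a slope of 1. This stands: the loss is in efficiency, not validity.
2. **Visit-specific comparisons are planned.** The t-tests cover each timepoint, and the ANCOVA is itself aimed at change at testing and follow-up timepoints. A group-by-time term is unstated rather than excluded. With change as the outcome, the group effect already asks whether change differs between arms. This stands in part: the comparisons exist, but without baseline adjustment and without one designated primary.
3. **Averaging need not hurt.** A reader might infer that the primary test is badly underpowered. That conclusion needs an assumed effect that fades after week 12. Under the same assumptions a sustained effect gives the averaged test more power than a week-12 test, and the documents do not say which pattern to expect. This stands.
4. **Nobody is said to be excluded.** A reader might infer that incomplete participants are dropped and the intention-to-treat statement is contradicted. The protocol names no fitting method and no exclusion, and the one-row-per-visit fit implied by time as a covariate would keep most of them. Detailed missing-data rules may also sit in an analysis plan that is not shown. What remains is that the model as described does not secure the claim.

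**Conclusion.** The point holds in this form and should be fixed. As written, the primary model gives one group difference averaged from week 6 to 24 months, while the sample size concerns 12-week change, and no single visit is named as decisive.

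The firm quantitative result is the precision lost by fixing the baseline slope at 1. Adjustment would cut the variance by 35%, 25% or 15% at r = 0.3, 0.5 or 0.7, given equal variances. That takes power from about 80% to about 90% at an SD of 18.5, r = 0.5, 25 per group and 15 points. Neither the SD nor r is stated in the protocol.

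Whether averaging over visits costs or gains power is not established; it depends on how the effect behaves after week 12. The intention-to-treat claim is left unsecured, not contradicted.

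**What to change.** Replace the model description with a linear mixed model for the repeated VISA-A scores in all randomised participants. Include baseline VISA-A as covariate, visit as a categorical within-participant factor, group, and group-by-visit. Take the between-group contrast at week 12, the visit behind the sample size, as the primary test with its 95% confidence interval, and the other visits as secondary. State that participants with any follow-up score contribute. Report within-group changes descriptively. The separate t-tests on VISA-A are then no longer needed.

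The cost is analysis wording and a few lines of R, with no new data. The one statistical price is slightly lower power than the visit-averaged test if the effect is constant over time: about 90% against 95% in the illustration above.
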